### **Six months visit**

After the end of the intervention, participants will be invited for a third visit. The procedure is the same as that of the second visit. However, participants will not be taking part in an intervention while wearing the accelerometer. Participants will be asked to return the process evaluation questionnaires as well as the accelerometer, either by delivering it to the office of one of the researchers or returning it by post (pre-paid by the research team).

### **Follow up visit**

Six months after the intervention end, so twelve months after the intervention start, there will be one last follow-up visit. The procedure is again the same as that of the second and third visit, except that participants will not have to complete a process evaluation questionnaire. Again, we will ask participants to return the accelerometers by delivering it to the office of one of the researchers or by returning it by post (pre-paid by the research team).

[figure not shown]

Figure 1. Procedure

## 6. Statistical analysis plan

### 6.1. Hypotheses

#### Primary endpoint:

We hypothesize that the cognitively enriched walking program will have more beneficial effects on cognitive functioning compared to the other conditions at 6 months and 12 months.

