## 1. Introduction

Dementia currently affects more than 47 million people worldwide, its prevalence is forecasted to triple by 2050, and it has been reported to be one of the most costly disorders in Belgium.

There is good scientific evidence that the cognitive impairments associated with the development of dementia can be lessened or even reversed thanks to the plasticity of the brain (rewiring). Recent research has shown that physical activity combined with performing cognitively challenging tasks is a very potent way to induce this rewiring of the brain, which can enable people to improve their cognitive functions. Yet, so far, these studies are mainly limited to controlled laboratory conditions. Our team developed a real-life cognitively enriched walking program, with input from experts and end-users.

In this study, we will examine the added value of enriching physical activity (walking) with cognitive exercises in improving cognition of older adults by conducting a six-month community-based randomized controlled trial. We will also examine the longer term effectiveness in a follow-up measurement visit six months after the program. We will focus on the following outcomes: cognitive functioning (i.e., objective, subjective and cognitive activity), psychosocial wellbeing (i.e., loneliness, social support, depressive symptomatology, positive wellbeing and expectations regarding aging), physical activity (i.e. both objective and subjective) and general health.

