## 2. Study design

To evaluate the effects of the cognitively enriched walking program on cognitive functioning (primary outcome), physical activity and psychosocial wellbeing (secondary outcomes), a randomized controlled trial (RCT) will be conducted. The intervention period will be 6 months, with measurements conducted at baseline, 3 months (mid-intervention), 6 months (post-intervention) and 12 months (follow-up). The interventions and measurements will take place at 2 university campuses in Belgium (Ghent and Leuven).

Participants will be allocated to one of the following intervention arms with a 1:1:1 allocation ratio: (1) cognitively enriched walking program, (2) walking program without enrichment, (3) passive control group. An investigator not involved in running the trial will generate the randomization sequence stratified by location (Ghent/Leuven) and availability (2 scheduling options for each location) using a statistical software program. Allocation will be disclosed to the researchers and participants only after completion of baseline measurements, ensuring double-blind data collection at baseline.

Furthermore, a process evaluation will be embedded in the RCT, using a mixed-methods design, and thus comprises questionnaires and focus group interviews. Questionnaires will be completed mid-intervention and post-intervention, focus groups will be conducted post-intervention.

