The PA group will walk for approximately the same amount of time and distance as the PA+CA group, but will not perform cognitive exercises. The coach will supervise and guide the group walk. These participants will also be asked to register the amount of individual walks they perform in a personal log-book.

The passive CG will not receive an intervention. Participants will be informed that they are assigned to the control group.

Participants will receive a letter at home with information about the intervention group they are allocated to (i.e. when will the sessions take place, where will they take place, contact information of the coach). Participants will be asked to be present for as many sessions as possible, but given the real-life context of this study, we will have the coaches track the attendance (in both the PA+CA and PA groups) so we can account for this in the analyses. The control group will receive information about why the use of a control group is important in intervention studies to keep them motivated to attend the following measurement sessions.

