### 6.2. Sample size

An a priori power calculation was conducted in G\*Power 3.1. With an estimated effect size of 0.30 (average effect size for comparison between PA+CA and control across 3 meta-analyses of Zhu et al. (2016), Gavelin et

al. (2021) and Gheysen et al. (2018)),  $\alpha=0.05$ , power=0.80, a sample size of 124 would be sufficient to detect differences between the conditions. Assuming a 20% dropout rate, a total of 149 participants will be recruited.

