The outcomes are measured repeatedly at different time points, and are nested within individuals. This implies our data has a two-level structure, and this calls for an analysis technique taking into account the correlation between observations from the same person (Hoffman & Walters, 2022). Therefore, linear mixed models with random intercepts will be used, to take into account that each individual participant has a different starting point. Time (baseline, 3m, 6m and 12m) and condition (PA+CA, PA only, CG), and their interaction will be included as fixed effects.

Models with different levels of adjustment will be run: (1) crude model, (2) partially adjusted model including age, sex and education as covariates, and (3) fully adjusted model including age, sex, education, baseline PA and baseline CA as covariates. Model fit indices will be used to choose the models with the best fit.

In case of significant effects, post-hoc pairwise comparisons will be conducted to examine differences in the estimated marginal means of the outcome at T0, T1, T2 and T3 between 1) WALK+ vs. WALK-only and 2) WALK+ vs. CONT, but also the changes from T0 to T1, T0 to T2, T0 to T3, T1 to T2 and T2 to T3 for each group (WALK+, WALK-only and CONT). The p-values will be corrected for multiple testing.

The analysis will be conducted for the intention-to-treat and per protocol populations.

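### The contrast that answers the trial's question, enriched walking versus walking only, is not named as decisive and is tested only post hoc behind an unspecified gate

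*Combined protocol and SAP*

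**What the plan says.** The Introduction states the question: "we will examine the added value of enriching physical activity (walking) with cognitive exercises in improving cognition of older adults". Section 2 is broader and names no comparator; its aim begins "To evaluate the effects of the cognitively enriched walking program on cognitive functioning (primary outcome". Participants are randomised to three arms "with a 1:1:1 allocation ratio".

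Section 4 gives both walking arms the same format: coached groups, two sessions a week, an encouraged individual session, a log-book, and roughly equal walking time and distance. Of the third arm it says: "The passive CG will not receive an intervention. Participants will be informed that they are assigned to the control group".

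The primary hypothesis (section 6.1) is that "the cognitively enriched walking program will have more beneficial effects on cognitive functioning compared to the other conditions at 6 months and 12 months". Section 6.2 sizes the trial "With an estimated effect size of 0.30 (average effect size for comparison between PA+CA and control across 3 meta-analyses".

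Section 6.4 fits a mixed model with condition, time and their interaction. If there are significant effects (which ones is not said), it goes on to post-hoc comparisons between "1) WALK+ vs. WALK-only and 2) WALK+ vs. CONT". It promises a multiplicity correction but names neither the method nor the family. No section names a primary contrast, a testing order or a success rule.

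**The concern.** Two separate things are at stake.

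**What may be concluded.** WALK+ versus control combines enrichment with walking, contact with a coach and group, and participants' knowledge of whether they are in a programme. If WALK+ beats control and is no better than WALK-only, nothing has been shown about enrichment. The walking-only arm exists to make that distinction, yet no rule gives it the deciding role.

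**Whether the key contrast gets a fair test.** WALK+ versus WALK-only is not tested in its own right. It waits for an omnibus result that also depends on the control arm, and it then shares its correction with the control contrast. A real enrichment effect can be lost at either step.

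**Working it through.** **Step 1. What each contrast estimates.** Let *w* be the effect of the walking programme against control and *e* the extra effect of enrichment.
- WALK+ minus WALK-only = *e*
- WALK+ minus CONT = *w* + *e*

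With *e* = 0 the second contrast equals *w*. Multiplicity correction cannot repair this, because a significant result there reflects a real walking effect and is not a false positive.

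**Step 2. Inputs.**
- Effect 0.30 (section 6.2). It is given only for enriched walking versus control and its metric is not stated. I treat it as SD units, and applying it to *w* or *e* alone is my assumption.
- Evaluable sample 124 (section 6.2): 124 / 3 = 41.3, so 41 per arm. Recruited 149: 149 / 3 = 49.7, so about 50 per arm.
- Alpha 0.05, taken as two-sided because section 6.4 plans 95% intervals.

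The stated inputs do not determine 124, since the test family, effect metric and within-person correlation are missing. For example, a three-group one-way ANOVA with f = 0.30 needs 111 in total, and a two-arm comparison with d = 0.30 needs 175 per arm. The 149 is 124 × 1.20 = 148.8, rounded up. Nothing below depends on how 124 was reached.

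**Step 3. Power of one direct two-arm comparison.** The noncentrality is d × √(n/2). At n = 41 it is 0.30 × √20.5 = 1.36, on 80 degrees of freedom.

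| Per arm | Alpha 0.05 | Alpha 0.025 |
|---|---|---|
| 41 | 0.269 | 0.183 |
| 50 | 0.318 | 0.224 |

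These are powers to detect a true 0.30 SD difference between any two arms. The difference detectable with 80% power at 41 per arm is about (1.96 + 0.84) × √(2/41) = 0.62 SD.

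**Step 4. The plan's route when enrichment adds nothing** (*w* = 0.30, *e* = 0). This was simulated for one composite with four visits and 41 per arm. The gate is a significant condition-by-time interaction. Then come the two between-arm contrasts in change from baseline to 6 months, Bonferroni-corrected (0.025 each). WALK+ versus CONT is significant in about 11% of trials at within-person correlation 0.5 and 23% at 0.7.

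A simpler version uses a three-arm F test at one time point and baseline correlation 0 to 0.7. It gives 17-34% for the control contrast and about 1% for WALK+ versus WALK-only. Over four composites and two time points (assumed correlations 0.4 and 0.6), with Bonferroni over all 4 × 2 × 2 = 16 contrasts, at least one control contrast is significant in 25-50%.

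**Step 5. The plan's route when only enrichment works** (*w* = 0, *e* = 0.30). With the SD at each visit set to 1, the SD of a change score is √(2(1 − ρ)). That is 1.00 at ρ = 0.5 and 0.775 at ρ = 0.7, so the standardised differences are 0.30 and 0.30 / 0.775 = 0.39.

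| Correlation | WALK+ vs WALK-only tested directly, alpha 0.05 | Gated, Bonferroni over two |
|---|---|---|
| 0.5 | about 27% | about 11% |
| 0.7 | about 42% | about 22% |

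Section 6.4 also lists other visits and within-arm changes. A correction family that included them would lower the right-hand column further.

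**The case against.** **The hypothesis already requires both arms to be beaten.** The other conditions are two, and the plain sense of the plural is both. On that reading a control-only win fails the hypothesis, and if enrichment adds nothing the chance of support is about 1%. This is the more natural reading and it stands. What remains is that no success rule in section 6.4 says so.

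**The key contrast is already planned, and listed first.** True: no analysis is missing, and a null WALK+ versus WALK-only result would appear beside any control win, provided the gate opened. But list order is not a decision rule.

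**The control comparison has a legitimate purpose.** Section 2's aim concerns the programme as a whole, and WALK+ versus control answers it. The point is what that comparison may be used to claim, not whether it belongs in the trial.

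**Two stronger inferences are not supported.** A reader might infer that the plan will credit the cognitive exercises with a control-only win. No section says that; the plan only fails to exclude it. A reader might also take the 27% and 32% in step 3 as false-claim rates. They are ordinary power to detect a real walking-programme effect and leave out the gate and the correction. Even the 11-23% becomes an error only if a control win is then reported as added value.

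**Conclusion.** The point holds as a gap in the decision rule and an avoidable loss of power. It does not show that the plan adopts a wrong hypothesis. The Introduction's question is answered by one contrast, and the plan neither makes that contrast decisive nor tests it directly.

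At 41 per arm, for one composite at 6 months, the ambiguous outcome (a significant control contrast with zero added value) has a probability of about 11-23%. The gate and shared correction take power for the enrichment contrast from about 27% to 11%, or from 42% to 22%.

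These figures assume a 0.30 SD effect, within-person correlation of 0.5 to 0.7, an interaction gate and Bonferroni over two contrasts. None of these except the 0.30 is in the plan. The sizes move with the assumptions; the direction does not.

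**What to change.** In section 6.1, state that added value of enrichment will be concluded only if WALK+ versus WALK-only favours WALK+. WALK+ versus CONT may be required as well, or be reported as programme versus no programme, with a note that it does not separate enrichment from walking, group contact and expectation.

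In section 6.4, make WALK+ versus WALK-only a planned contrast tested whatever the omnibus result. Name the composite and time point it refers to, or the correction across them; without that the test is still not fully defined.

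The cost is a few sentences, with no new data or participants. There are two downsides to state openly:
- A win over control alone no longer confirms the primary hypothesis.
- Power for the enrichment contrast is low: about 27% at d = 0.30 and 41 per arm without baseline adjustment, against 175 per arm needed for 80%. The documents give no expected size for the enrichment effect alone, so this power should be reported with its assumption.

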#### Secondary endpoints:

We hypothesize that both the cognitively enriched walking program and the walking program without cognitive enrichment will have more beneficial effects on moderate-to-vigorous PA levels compared to the control group.

We hypothesize that both the cognitively enriched walking program and the walking program without cognitive enrichment will have more beneficial effects on psychosocial wellbeing compared to the control group.

#### Process evaluation:

For this endpoint, we do not have a predefined hypothesis. This will thus be an exploratory analysis.

### 6.2. Sample size

An a priori power calculation was conducted in G\*Power 3.1. With an estimated effect size of 0.30 (average effect size for comparison between PA+CA and control across 3 meta-analyses of Zhu et al. (2016), Gavelin et

al. (2021) and Gheysen et al. (2018)),  $\alpha=0.05$ , power=0.80, a sample size of 124 would be sufficient to detect differences between the conditions. Assuming a 20% dropout rate, a total of 149 participants will be recruited.

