### 6.4. Statistical analyses

#### General

For descriptive statistics, categorical data will be presented as percentages and counts, continuous data will be presented as means with standard deviations or medians with interquartile range in case of non normally distributed data.

For inferential statistics,  $\alpha$  will be set at 0.05, and 95% confidence intervals will be calculated. In case of multiple testing, a correction of the p-values will be used.

Covariates will be specified below and are selected based on theoretical knowledge.

Checks of assumptions will be performed, in case of non-normality, transformations of the variables or non-parametric tests will be used.

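### Section 6.2 gives no effect size or power for enriched walking versus walking alone, yet claims its sample size suffices for comparisons among the arms in general

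*Combined protocol and SAP*

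**What the plan says.** The Introduction sets the aim: "we will examine the added value of enriching physical activity (walking) with cognitive exercises in improving cognition of older adults". Section 4 gives the PA arm walking of similar duration and distance but no cognitive exercises, so PA+CA versus PA isolates the enrichment. Under Primary endpoint in section 6.1, the enriched program "will have more beneficial effects on cognitive functioning compared to the other conditions at 6 months and 12 months". That covers both PA and CG.

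The planned between-arm comparisons in section 6.4, Primary outcome, match this: "1) WALK+ vs. WALK-only and 2) WALK+ vs. CONT". They are made only after a significant effect, with p-values corrected for multiple testing.

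Section 6.2 uses one effect size, 0.30, described as the "average effect size for comparison between PA+CA and control across 3 meta-analyses", with alpha 0.05 and power 0.80. It concludes that "a sample size of 124 would be sufficient to detect differences between the conditions", and sets recruitment at 149 to allow for 20% dropout. It does not name the G*Power test, the effect metric or any within-person correlation. Nowhere do the documents give an effect size or a power for PA+CA versus PA.

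**The concern.** The effect size comes from one of the two primary contrasts, but the conclusion about sample size is worded for the arms in general. A reader will assume that the enrichment contrast is covered. If walking alone helps cognition at all, PA+CA differs less from PA than from a passive control, so the contrast that answers the study's question is the harder one to detect.

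What is at stake is how a null result is read. If PA+CA versus PA is not significant in a trial described as large enough to show differences among its arms, the natural conclusion is that enrichment adds nothing. The plan has not shown that the trial could support that conclusion.

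**Working it through.** **Inputs**
- Effect 0.30 for PA+CA versus control; alpha 0.05; power 0.80; N = 124; recruitment 149 (section 6.2).
- Allocation 1:1:1 (section 2): 124/3 = 41.3 per arm; 149/3 = 49.7 per arm.
- Sidedness is not stated. Two-sided is assumed, because section 6.4, General, says "95% confidence intervals will be calculated".
- The correlation between baseline and follow-up is not given. I use none (unadjusted) and 0.7 (an assumption).

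**Step 1: can 124 be reproduced?** Not from the stated inputs alone.
- Two-sample comparison, d = 0.30: n per arm = 2(1.960 + 0.842)²/0.30² = 174.4, so 175 per arm and 350 for two arms.
- One-way ANOVA or ANCOVA, f = 0.30: 111 for three groups, 90 for two.
- Repeated-measures interaction, f = 0.30/2 = 0.15, four time points, noncentrality f²·N·4/(1 − ρ): two groups with ρ = 0 need 123, or 124 with equal groups; three groups with ρ = 0.2 need 124, or 126 with equal groups.

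So 124 can be reached, but only with inputs that the plan does not state. It is under-specified, not shown to be wrong.

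**Step 2: does 0.30 carry over to PA+CA versus PA?** On a common scale,

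(PA+CA − CG) = (PA+CA − PA) + (PA − CG).

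If the pooled controls were passive, as CG is here, 0.30 applies to PA+CA versus PA only when walking alone has no cognitive effect. It could also carry over if the pooled controls were themselves active. The plan states neither.

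**Step 3: power for two arms of 41.3 at one visit, taking 0.30 as a standardised mean difference.**

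Power = Φ( d·√(n/2)/√(1 − r²) − 1.960 ), with √(41.33/2) = 4.546 and √(1 − 0.7²) = 0.714.

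| Assumed d | Unadjusted | r = 0.7 |
|---|---|---|
| 0.30 | Φ(1.364 − 1.960) = 28% | Φ(1.910 − 1.960) = 48% |
| 0.20 | Φ(0.909 − 1.960) = 15% | Φ(1.273 − 1.960) = 25% |
| 0.15 | Φ(0.682 − 1.960) = 10% | Φ(0.955 − 1.960) = 16% |

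The noncentral t distribution gives 27% instead of 28% in the first cell. The values of d below 0.30 are illustrative, since the documents give none for this contrast.

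**Step 4: difference detectable with 80% power.**
- Unadjusted: 2.802 × √(2/41.33) = 0.62.
- With r = 0.7: 0.616 × 0.714 = 0.44.
- If all 149 were retained (49.7 per arm), unadjusted: 0.56, with 32% power at d = 0.30.
- Correlation needed for 80% power at d = 0.30: 1 − r² = (0.30/0.616)² = 0.237, so r is about 0.87.

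**Step 5: the other metric.** If 0.30 is Cohen's f, the two-group equivalent is d = 2 × 0.30 = 0.60. Power is then Φ(0.60 × 4.546 − 1.960) = Φ(0.768) = 78% (77% by noncentral t), but only if a difference of 0.60 applied to PA+CA versus PA.

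All figures precede the planned multiplicity correction, which would lower them.

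**The case against.** The strongest reply has four parts.

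1. **PA+CA versus CG is also a primary contrast.** This stands. A reader might infer that the trial was sized on the wrong comparator. The documents do not support that: the primary hypothesis names both comparators, section 6.4 gives neither priority, and the calculation addresses one of the two.

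2. **The sufficiency sentence may refer to an overall or interaction test.** The pairwise comparisons come later and are conditional on a significant effect, so the plan does not literally promise 80% for each pair. This also stands. But the sentence does not say which test it means, and an overall test would still leave the enrichment contrast without a stated power.

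3. **The metric and the make-up of the pooled controls are unknown.** This stands, and it limits the arithmetic. A reader might take 80% at 0.30 as given for PA+CA versus PA and scale it down for an assumed walking effect. That would overstate power under a standardised mean difference, since two arms of about 41 do not reach 80% at 0.30 in the first place. The subtraction would also fail if the pooled controls were active.

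4. **Confidence intervals are already planned, and nothing says a null result will be read as no effect.** Both are true. What is missing is a rule for interpreting that result, while the sufficiency claim invites the wrong reading.

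None of these supplies an effect size or a power for PA+CA versus PA.

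**Conclusion.** The point holds as one about an unsupported power statement. The plan does not show that the trial has 80% power for PA+CA versus PA, the primary contrast that answers its stated aim.

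Under a standardised mean difference, two-sided 0.05 and about 41 per arm at one visit, power at 0.30 is about 28% unadjusted and 48% with an assumed baseline correlation of 0.7. It falls to 10–16% at 0.15. The detectable difference is roughly 0.44 to 0.62. Under Cohen's f the picture is much better, at 77–78%, but that requires a difference of about 0.60 between two arms that both walk, which nothing in the plan supports.

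The Step 3 figures apply equally to PA+CA versus CG at the same difference, so it would be a mistake to conclude that 80% is established for that pair. Nor do the documents show that 124 is an error or that the three-arm design is unsuitable. The correction should be made, but it concerns what the plan claims and how a null result is interpreted.

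**What to change.** In section 6.2:
- State the G*Power test, the effect metric, the number of groups and time points, and the assumed correlation behind 124. Say what kind of control the 0.30 was measured against.
- Remove the general claim of sufficiency for differences among the arms.
- For WALK+ versus WALK-only, and separately for WALK+ versus CONT, give the difference detectable with 80% power and the power over a stated range of effects at the planned number per arm. Say whether multiplicity correction is included.

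In section 6.4, Primary outcome:
- State that a non-significant WALK+ versus WALK-only result will be interpreted from its already planned 95% confidence interval and not as evidence of no added value.

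The cost is a few sentences and one short calculation. No extra participants and no change to the analysis model are needed. The downside is that the stated power will look less favourable.

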## 4. Interventions

As mentioned above, there will be three intervention arms: 1) a cognitively enriched walking program (Physical Activity (PA)+Cognitive Activity (CA)), 2) a walking program without cognitive enrichment (Physical Activity (PA) only) or 3) a passive control group (CG). The passive CG will receive no intervention program. Both the PA+CA and the PA program are group-based and will have a duration of six months (i.e. 24 weeks), with a frequency of two group sessions a week. All group sessions will last for approximately one hour and take place in groups of twelve or thirteen people supervised by a certified coach. Participants in both intervention groups (PA+CA and PA) will be encouraged to do one individual session every week, as well.

The PA+CA group will perform cognitive exercises while walking. One cognitively enriched walking session can be divided in three parts: (1) 5-10 minutes of brisk walking, (2) approximately 30-40 minutes of cognitive exercises while walking and (3) 5-10 minutes of cooling down (i.e. time for small talk or rest and relaxation). Cognitive exercises are exercises that are cognitively challenging and focus on multiple cognitive functions (i.e. attention, memory, executive functions, language, creative thinking) and can be performed while walking. Some examples are: planning a route, solving riddles, noticing, word fluency, bingo (i.e. noticing things along the walk),... These cognitive exercises have been developed in agreement with experts and the target population (Marent et al., 2021). Every cognitively enriched walking session, two to three cognitive exercises will be explained by the coach and performed by the participants. To this end, the coach receives a standardized manual with explanations of the different cognitive exercises. Furthermore, the coach will make sure that participants keep moving while performing the cognitive exercises. For the individual sessions, participants of the PA+CA group will receive practice cards with simplified instructions for all cognitive exercises that can be performed alone, with their partner, friends, or even grandchildren. Participants will be asked to register the number of individual cognitively enriched walks they perform in a personal log-book.

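### Recruiting 149 does not leave 124 participants after 20% dropout: about 119 remain, and 124 would need 155 recruits

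*Combined protocol and SAP*

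**What the plan says.** Section 6.2 (Sample size) reports an a priori G*Power calculation with an effect size of 0.30, α = 0.05 and power of 0.80, and concludes that "a sample size of 124 would be sufficient to detect differences between the conditions". The next sentence turns this into a recruitment target: "Assuming a 20% dropout rate, a total of 149 participants will be recruited". The inflation formula is not shown. No other section gives a different recruitment total or a different dropout rate.

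Two other parts of the plan bear on the remedy. Section 2 allocates 1:1:1 to three arms, stratified by location (two) and scheduling option (two per location). Section 4 says the group sessions "take place in groups of twelve or thirteen people supervised by a certified coach", and the focus-group part of Section 5.2 counts four groups in each walking arm.

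**The concern.** A dropout allowance has one purpose: the number left after the assumed loss should be at least the number the power calculation requires. The assumed loss is a proportion of the people who enter the trial, so the requirement must be divided by the proportion expected to stay. Adding 20% to the requirement is a common slip, and it always gives too few, because the 20% is then taken from a larger number than the one it was added to.

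If that happened here, the plan misses its own size requirement under its own dropout assumption, and the stated power of 0.80 does not apply to the number it expects to keep. The primary hypothesis in Section 6.1 concerns 6 and 12 months, so the later comparisons carry most of the accumulated dropout.

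**Working it through.** **Inputs, all from Section 6.2**

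- Required sample after dropout: 124 in total
- Assumed dropout: 20%
- Recruitment target: 149 in total
- Power 0.80 and α 0.05 (sidedness not stated; two-sided assumed in step 5)

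**1. Reproduce the plan's figure.** Adding 20% to the requirement gives 124 × (1 + 0.20) = 148.8, which rounds up to 149. The match is exact. The method is inferred from that match, because the plan does not print it.

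**2. Standard inflation.** Required / (1 − dropout) = 124 / 0.80 = 155. Check: 155 × 0.80 = 124.

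**3. What 149 delivers at 20% dropout.** 149 × 0.80 = 119.2, so about 119. The shortfall is 124 − 119 = 5 participants retained, or 155 − 149 = 6 recruits.

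**4. Dropout that 149 can absorb.** (149 − 124) / 149 = 25 / 149 = 16.8%.

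**5. Effect on power.** Take the plan's statement of 80% power at 124 as given and scale the standardised effect by the square root of the sample size. This uses a two-sided normal approximation for a single contrast:

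- At 124: 1.96 + 0.84 = 2.80
- At 119: 2.80 × √(119/124) = 2.80 × 0.980 = 2.74
- 2.74 − 1.96 = 0.78, which corresponds to power of about 78%

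The plan's own power calculation cannot be rerun to confirm this. It does not give the G*Power test family, the effect-size metric, the number of measurements or the correlation between them. As an illustration under an assumed setting, a three-group one-way ANOVA with 0.30 read as Cohen's f gives power of 0.849 at 124 and 0.832 at 119. That setting needs only 111 participants for 80% power, so it is probably not the one used, but the drop is of similar size (1.7 percentage points).

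**6. Room for a larger target.** Two locations × two scheduling options × three arms = 12 cells.

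| Recruited | Split 1:1:1 | Average per cell | Capacity per walking arm (4 groups × 13) |
|---|---|---|---|
| 149 | 50 / 50 / 49 | 12.4 | 52 |
| 155 | 52 / 52 / 51 | 12.9 | 52 |

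At 155 each walking arm could hold 52 people and would be filled exactly, or left one place short if it is the arm of 51.

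**The case against.** Four points can be made for the plan.

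- **Dropouts are not lost entirely.** Section 6.3 includes everyone assigned in the intention-to-treat analysis, and Section 6.4 fits a linear mixed model to baseline, 3, 6 and 12 months. Such a model can use the earlier visits of someone who leaves later. The effective loss therefore lies between nothing and the full five participants, depending on when people leave. This stands, and it makes 78% close to a worst case. It does not reconcile the figures, because the plan chose to inflate for dropout and the inflation does not reach its target.
- **The shortfall is small.** Five of 124 is 4%, the 20% has no stated source, and 149 still covers dropout up to 16.8%. This also stands. The error does not threaten the design or the interpretation of the trial.
- **The 20% may have been meant as a share of the 124.** On that reading about 25 people are lost from 149, which is a dropout rate of 16.8%. The sentence would still state the wrong rate and would need the same correction.
- **The ×1.2 step is not documented.** That is correct. However, the contradiction between 124, 20% and 149 holds however 149 was obtained.

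**Conclusion.** The concern holds. On the plan's own figures, 149 recruits at 20% dropout leave about 119, which is 5 short of 124. Keeping 124 would take 155, and 149 allows for 16.8% dropout.

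This part uses only numbers in Section 6.2 and the usual meaning of a dropout rate. The power figure of about 78% rests on two further assumptions: that power really is 80% at 124, and that those who drop out contribute nothing. With partial data in the mixed model the loss is smaller. The finding takes 124 as given and makes no judgement on how it was derived.

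The sample-size statement should be corrected, but the trial's validity is not in question.

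**What to change.** **Minimum change.** Replace the last sentence of Section 6.2 with wording such as: *A total of 149 participants will be recruited. This retains 124 if dropout is at most 16.8%; at 20% dropout about 119 would remain, with power of [x].* The value of x should come from the sponsor's own G*Power settings, and those settings should be stated beside it. The approximation above suggests about 78%. This costs one sentence and one rerun of an existing calculation.

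**Optional change, if recruitment is still open and the sponsor wants 124 after 20% dropout.** Set the target at 155, six more people. No extra group or coach is needed on paper. But the eight walking groups hold at most 8 × 13 = 104, and two thirds of 155 is 103.3. Nearly every location-by-schedule stratum would have to fill to 13 per walking arm, so the feasibility of this should be checked before the target is changed.
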